| 
8. Sensory: Sensation or grimace to pinprick when tested, or withdrawal from noxious stimulus in the obtunded or aphasic patient. Only sensory loss attributed to stroke is scored as abnormal and the examiner should test as many body areas (arms [not hands], legs, trunk, face) as needed to accurately check for hemisensory loss. A score of 2, 'severe or total sensory loss', should only be given when a severe or total loss of sensation can be clearly demonstrated. Stuporous and aphasic patients will, therefore, probably score 1 or 0. The patient with brainstem stroke who has bilateral loss of sensation is scored 2. If the patient does not respond and is quadriplegic, score 2. Patients in a coma (item 1a=3) are automatically given a 2 on this item.
 | 
0= Normal; no sensory loss.
 
1= Mild-to-moderate sensory loss; patients feels pinprick is less sharp or is dull on the affected side; or there is a loss of superficial pain with pinprick, but patient is aware of being touched.
 
2= Severe to total sensory loss; patient is not aware of being touched in the face, arm and leg.
                                                                                                 |
| 
9. Best language: A great deal of information about comprehension will be obtained during the preceding sections of the examination. For this scale item, the patient is asked to describe what is happening in the attached picture, to name the items on the attached naming sheet and to read from the attached
                                                                                                                                                                                                                                                                                                                                                                                                                                                                 | 
0= No aphasia; normal
 
1= Mild-to-moderate aphasia; some obvious loss of fluency or facility of comprehension, without significant limitation on ideas expressed or form of expression. Reduction of
                                                                                                                                                                                                                                       |

|                                                                                                                                                                                                                                                                                                                                                                                                                                                                                                                                                                                                  |                                                                                                                                                                                                                                                                                                                                                                                                                                                                                                                                                                                                                                                             |
|--------------------------------------------------------------------------------------------------------------------------------------------------------------------------------------------------------------------------------------------------------------------------------------------------------------------------------------------------------------------------------------------------------------------------------------------------------------------------------------------------------------------------------------------------------------------------------------------------|-------------------------------------------------------------------------------------------------------------------------------------------------------------------------------------------------------------------------------------------------------------------------------------------------------------------------------------------------------------------------------------------------------------------------------------------------------------------------------------------------------------------------------------------------------------------------------------------------------------------------------------------------------------|
| 
list of sentences. Comprehension is judged from responses here, as well as to all of the commands in the preceding general neurological exam. If visual loss interferes with the tests, ask the patient to identify objects placed in the hand, repeat, and produce speech. The intubated patient should be asked to write. The patient in a coma (item 1a=3) will automatically score 3 on this item. The examiner must choose a score for the patient with stupor or limited cooperation, but a score of 3 should be used only if the patient is mute and follows no one-step commands.
 | 
speech and/or comprehension, however, makes conservation about provided materials difficult or impossible. For example, in conversation about provided materials, examiner can identify picture or naming card content from patient's response.
 
2= Severe aphasia; all communication is through fragmentary expression; great need for inference, questioning, and guessing by the listener. Range of information that can be exchanged is limited; listener carries burden of communication. Examiner cannot identify materials provided from patient response.
 
3 = Mute, global aphasia: no usable speech or auditory comprehension.
 |
| 
10. Dysarthria: If patient is thought to be normal, an adequate sample of speech must be obtained by asking patient to read or repeat words from the attached list. If the patient has severe aphasia, the clarity of articulation of spontaneous speech can be rated. Only if patient is intubated or has other physical barriers to producing speech, the examiner should record the score as untestable (UN), and clearly write an explanation for this choice. Do not tell the patient why he or she is being tested.
                                                          | 
0= Normal.
 
1= Mild-to-moderate dysarthria; patient slurs at least some words and, at worst, can be understood by some difficulty.
 
2= Severe dysarthria: patient's speech is so slurred as to be unintelligible in the absence of or out of proportion to any dysphasia, or is mute/anarthric.
 
UN = Intubated or other physical barrier.
                                                                                                                                                                                                                                                                                         |
| 
11. Extinction and Inattention (formerly Neglect): Sufficient information to identify neglect may be obtained during the prior testing. If the patient has a severe visual loss preventing visual double simultaneous stimulation, and the cutaneous stimuli are normal, the score is normal. If the patient has aphasia but does appear to attend to both sides, the score is normal. The presence of visual spatial neglect or anosagnosia may also be taken as evidence of abnormality. Since the abnormality is scored only if present, the item is never untestable.
          | 
0= No abnormality.
 
1= Visual, tactile, auditory, spatial, or personal inattention or extinction to bilateral simultaneous stimulation in one of the sensory modalities.
 
2= Profound hemi-inattention or extinction to more than one modality; does not recognize own hand or orients to only one side of space.
                                                                                                                                                                                                                                                                                                                        |

**Appendix Table 4. EuroQoL 5D-5L**

Under each heading, please tick the ONE box that best describes your health TODAY.

**Mobility**

- I have no problems in walking about ☐
- I have slight problems in walking about ☐
- I have moderate problems in walking about ☐
- I have severe problems in walking about ☐
- I am unable to walk about ☐

**Self-care**

- I have no problems washing or dressing myself ☐
- I have slight problems washing or dressing myself ☐
- I have moderate problems washing or dressing myself ☐
- I have severe problems washing or dressing myself ☐
- I am unable to wash or dress myself ☐

**Usual activities (e.g. work, study, housework, family or leisure activities)**

- I have no problems doing my usual activities ☐
- I have slight problems doing my usual activities ☐
- I have moderate problems doing my usual activities ☐
- I have severe problems doing my usual activities ☐
- I am unable to do my usual activities ☐

**Pain/discomfort**

- I have no pain or discomfort ☐
- I have slight pain or discomfort ☐
- I have moderate pain or discomfort ☐
- I have severe pain or discomfort ☐
- I have extreme pain or discomfort ☐

**Anxiety/depression**

- I am not anxious or depressed ☐
- I am slightly anxious or depressed ☐
- I am moderately anxious or depressed ☐
- I am severely anxious or depressed ☐
- I am extremely anxious or depressed ☐

- We would like to know how good or bad your health is TODAY.
- This scale is numbered from 0 to 100.
- 100 means the best health you can imagine.  
0 means the worst health you can imagine.
- Mark an X on the scale to indicate how your health is TODAY.
- Now, please write the number you marked on the scale in the box below.

YOUR HEALEH TOADY =

[figure not shown]

**Appendix Table 5. Heidelberg bleeding classification**

Symptomatic intracranial hemorrhage (SICH): new intracranial hemorrhage detected by brain imaging associated with any of the items below:

1.  $\geq 4$  points decline in the total NIHSS at the time of diagnosis compared to immediately before worsening. Note that a 4 points change is not compared with the baseline admission NIHSS score but instead to the immediate predeterioration neurological status

2.  $\geq 2$  point decline in one NIHSS category. The rationale for this is to capture new hemorrhages that produce new neurological symptoms, making them clearly symptomatic but not causing worsening in the original stroke territory. For example, a new remote hemorrhage in the contralateral occipital lobe may cause new hemianopia that is clearly symptomatic but the patient will not have worsening of  $\geq 4$  points on the NIHSS score

Leading to intubation/hemicraniectomy/EVD placement or other major medical/surgical intervention.

3. Absence of alternative explanation for deterioration

| Anatomic Description of Intracranial Hemorrhages |                                                                                                      |                                                                                  |
|--------------------------------------------------|------------------------------------------------------------------------------------------------------|----------------------------------------------------------------------------------|
| Class                                            | Type                                                                                                 | Description                                                                      |
| 1                                                | Hemorrhagic transformation of infarcted brain tissue                                                 |                                                                                  |
| 1a                                               | HI1                                                                                                  | Scattered small petechiae, no mass effect                                        |
| 1b                                               | HI2                                                                                                  | Confluent petechiae, no mass effect                                              |
| 1c                                               | PH1                                                                                                  | Hematoma within infarcted tissue, occupying $<30\%$ , no substantive mass effect |
| 2                                                | Intracerebral hemorrhage within and beyond infarcted brain tissue                                    |                                                                                  |
|                                                  | PH2                                                                                                  | Hematoma occupying 30% or more of the infarcted tissue, with obvious mass effect |
| 3                                                | Intracerebral hemorrhage outside the infarcted brain tissue or intracranial-extracerebral hemorrhage |                                                                                  |
| 3a                                               |                                                                                                      | Parenchymal hematoma remote from infarcted brain tissue                          |
| 3b                                               |                                                                                                      | Intraventricular hemorrhage                                                      |
| 3c                                               |                                                                                                      | Subarachnoid hemorrhage                                                          |
| 3d                                               |                                                                                                      | Subdural hemorrhage                                                              |

HI indicates hemorrhagic infarction; and PH, parenchymatous hematoma.

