### **7.3 Primary safety endpoint**

Rate of sICH within 48 hours from randomization (Heidelberg Bleeding Classification, Appendix 5)

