### **Primary Safety Endpoints**

Rate of symptomatic intracranial hemorrhage within 48 hours from randomization (Heidelberg Bleeding Classification).

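### The English and Chinese protocols define symptomatic intracranial haemorrhage (sICH), the primary safety endpoint, by different rules, and the Chinese appendix alone starts the 48 hours at EVT

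*Supplement*

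**What the plan says.** Section 7.3 of protocol v7.1 sets the primary safety endpoint as "Rate of sICH within 48 hours from randomization" and sends the reader to Appendix 5 for the definition. SAP v2.0 (sections 3 and 13) repeats the endpoint with the same time origin. It names the Heidelberg classification but gives no criteria.

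English Appendix Table 5 defines sICH as "new intracranial hemorrhage detected by brain imaging associated with any of the items below". The list then runs as follows:

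- Item 1: at least 4 "points decline in the total NIHSS at the time of diagnosis compared to immediately before worsening".
- Item 2: at least a 2 "point decline in one NIHSS category".
- An unnumbered line after item 2: "Leading to intubation/hemicraniectomy/EVD placement or other major medical/surgical intervention".
- The last item: "3. Absence of alternative explanation for deterioration".

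The Chinese protocol (Appendix 5) states that all of three conditions must be met together:

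- an intracranial haemorrhage of any Heidelberg class, shown on imaging within 48 hours after endovascular treatment;
- clinical deterioration, by an NIHSS rise of at least 4 points, or a rise of at least 2 on any one item, or a major intervention such as intubation, decompressive craniectomy or ventricular drainage;
- no cause other than the haemorrhage that explains the deterioration.

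The Chinese synopsis and Chinese section 7.3 count the 48 hours from randomization.

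**The concern.** sICH is the primary safety endpoint and the whole of the secondary objective (section 2.2), so its case definition should be the same for every reader. Here the definition depends on the language of the protocol in hand. The cases on which the two texts split are plausible ones in this population: in a large infarct, swelling may cause the worsening while the follow-up scan shows minor haemorrhagic transformation. Scattered petechiae (HI1) already count as a bleed in both appendices. Such a patient is an sICH case under the literal English text and not under the Chinese text.

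The time origin is a second, smaller conflict. A window that starts at EVT has no starting point for patients given best medical management alone, and in the EVT arm it ends later than one that starts at randomization.

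**Working it through.** The documents state no sICH rate, power or margin, so there is no figure to reproduce. The check is a direct comparison of the two rules.

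**Same design.** The Chinese protocol plans 502 patients, with interim analyses at 168 and 336, a common odds ratio of 1.73 and a two-sided level of 0.046. These match English v7.1, section 10.1, so the conflict is not one between an old version and a new one.

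**Rules.** For a patient with a new intracranial bleed, take four yes/no flags:

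- A: total NIHSS worsening of at least 4
- B: worsening of at least 2 on one item
- C: major intervention
- N: no alternative explanation

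That gives 2^4 = 16 patterns.

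The Chinese rule is (A or B or C) and N. Of the 8 patterns with N present, 7 have at least one of A, B or C, so 7 patterns count as sICH.

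The English rule depends on how the unnumbered intervention line is read:

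| Reading of the intervention line | Literal English rule | Patterns counted as sICH | Disagreements with Chinese rule |
|---|---|---|---|
| A separate alternative | A or B or C or N | 15 | 15 − 7 = 8 |
| Ignored | A or B or N | 14 | 14 − 7 = 7 |
| A qualifier of item 2 | A or (B and C) or N | 13 | 13 − 7 = 6 |

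Subtraction is enough because every pattern that meets the Chinese rule has N present and so also meets each English reading. On the same time window, the literal English rule is always the wider one.

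**Where they split.** Six patterns differ under every reading:

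- the four with A present and N absent, that is, a worsening of 4 or more points with another explanation;
- the one with B and C present but A and N absent;
- the one with N alone, where no listed deterioration threshold is reached.

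**Time origin.** The places that state it compare as follows:

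| Place | 48 hours counted from |
|---|---|
| English synopsis and section 7.3 | randomization |
| SAP v2.0, sections 3 and 13 | randomization |
| Chinese synopsis and section 7.3 | randomization |
| Chinese Appendix 5, condition 1 | endovascular treatment |

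English Appendix Table 5 states no window of its own.

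**The case against.** The best defence is that the English list is a layout or translation fault and not a chosen rule. Its last item speaks of an explanation for deterioration, which presupposes a deterioration and reads naturally as a qualifier. The stray unnumbered line shows that the list is broken, and the Chinese text has the coherent structure. The plan also names a published classification, requires sites to train in it (section 13.2) and has a CEC review safety endpoints under its own charter (section 13.1). All of this is fair, and it makes it likely that an experienced adjudicator would apply the intended rule. It does not mend the text. Section 7.3 names Appendix 5 as the definition, the SAP adds nothing, and the charter is not shown.

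On timing, a reader might infer that the Chinese protocol as a whole runs the window from EVT and that the control arm therefore has no defined window. The documents do not support that. Every passage that states the endpoint, in either language, uses randomization, so the control-arm window is defined. What remains is one phrase that contradicts the rest and cannot apply to patients on medical management alone. Section 6 also asks for puncture within 1 hour of randomization; the procedure time that would complete the shift is not given.

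The use of the word decline for NIHSS worsening is a matter of copy-editing. Item 1 itself refers to worsening, so no one should score an improvement as sICH.

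**Conclusion.** The point holds as a conflict of definition. Read literally, the English and Chinese appendices give the primary safety endpoint two rules that disagree on 6 to 8 of 16 criterion patterns, and one phrase gives it a second time origin. The pattern count assumes the literal any-of reading of the English list and carries no frequency weights.

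A reader might go further and infer that the wider English rule inflates sICH in the EVT arm. The documents do not settle even the sign. Suppose, purely as an assumption, new bleeds in 30% of EVT and 15% of control patients:

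- With the same 10–20% of those bleeds accompanied by oedematous worsening in both arms, the wider rule adds 3–6 points to EVT (30% × 10–20%) and 1.5–3 points to control (15% × 10–20%).
- With the hemicraniectomy rates that section 1.1 cites from a 28-pair matched study (7% with EVT, 21% without, p=0.10) as a rough stand-in for oedema, it adds 30% × 7% = 2.1 points to EVT and 15% × 21% = 3.15 points to control, and the imbalance reverses.

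No excess in either arm should be claimed.

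This should be fixed, but it does not threaten the trial's main result. sICH enters neither the sample size (section 10.1) nor the interim boundaries, which use mRS 0–2 (section 10.4).

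**What to change.** Put one definition in both language versions of Appendix 5 and in the CEC charter. It should require all of:

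1. a new intracranial haemorrhage on imaging within 48 hours of randomization;
2. at least one of an NIHSS worsening of 4 or more points from the state just before deterioration, a worsening of 2 or more on one item, or a resulting major intervention (intubation, hemicraniectomy, ventricular drain or similar);
3. no alternative explanation for the deterioration.

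This makes absence of another explanation a required condition, turns the unnumbered intervention line into a clear alternative deterioration criterion, and replaces the EVT phrase in Chinese Appendix 5 with the randomization anchor used everywhere else. SAP section 13 should point to the agreed text.

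The cost is wording in two appendices, alignment of the charter, and submission of the amendment to the ethics committee (section 11.4). If cases have already been adjudicated, check which text was applied. Look again at bleeds with another recorded cause of worsening, bleeds below every deterioration threshold, and any event that falls between the two possible 48-hour cut-offs. If the charter already holds the agreed rule, only the appendices need to change. The sample size and interim boundaries are unaffected.

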### Appendix Table 6. Alberta Stroke Program Early CT Score (ASPECTS)

The Alberta Stroke Program Early CT Score (ASPECTS) is a semiquantitative method of estimation of infarct size with non-contrast CT during the acute phase. The territory of the middle cerebral artery is allotted 10 points. 1 point is subtracted for an area of early ischaemic change, such as focal swelling, or parenchymal hypoattenuation, for each of the defined regions. A normal CT scan has an ASPECTS value of 10 points. A score of 0 indicates diffuse ischaemia throughout the territory of the middle cerebral artery.

[figure not shown]

A=anterior circulation; P=posterior circulation; C=caudate; L=lentiform; IC=internal capsule; I=insular ribbon; MCA=middle cerebral artery; M1=anterior MCA cortex; M2=MCA cortex lateral to insular ribbon; M3=posterior MCA cortex; M4, M5, and M6 are anterior, lateral, and posterior MCA territories immediately superior to M1, M2, and M3, rostral to basal ganglia. Subcortical structures are allotted 3 points (C, L, and IC). MCA cortex is allotted 7 points (insular cortex, M1, M2, M3, M4, M5, and M6).

